## Abstract

**Background:**

Encephalitis/meningitis brings a heavy disease burden, and the origin of disease remains unknown in 30–40% of patients. It is greatly significant that combinations of nucleic acid amplification and autoimmune antibody testing improves the diagnosis and treatment of encephalitis/meningitis. Moreover, though several diagnostic methods are in clinical use, a recognized and unified diagnosis and treatment process for encephalitis management remains unclear.

**Methods:**

IMPROVE is a multicenter, open label, randomized controlled clinical trial that aims to evaluate the diagnostic performance, applications, and impact on patient outcomes of a new diagnostic algorithm that combines metagenomic next-generation sequencing (mNGS), multiplex polymerase chain reaction (PCR) and autoimmune antibody testing. The enrolled patients will be grouped into two parallel groups, multiplex PCR test plus autoimmune antibody group (Group I) or the mNGS plus autoimmune antibody group (Group II) with a patient ratio of 1:1. Both groups will be followed up for 12 months. The primary outcomes include the initial time of targeted treatment and the modified Rankin scale score on the 30th day of the trial. The secondary outcomes are the cerebrospinal fluid index remission rate on the 14th day, mortality rate on the 30th day, and an evaluation of diagnostic efficacy. The two groups are predicted to comprise of 484 people in total.

**Discussion:**

To optimize the roadmap of encephalitis/meningitis, precise diagnosis, and treatment are of great significance. The effect of rapid diagnosis undoubtedly depends on the progression of new diagnostic tests, such as the new multiplex PCR, mNGS, and examination of broad-spectrum autoimmune encephalitis antibodies. This randomized-controlled study could allow us to obtain an accurate atlas of the precise diagnostic ability of these tests and their effect on the treatment and prognosis of patients.

*Trial registration* ClinicalTrial.gov, NCT04946682. Registered 29 June 2021, ‘Retrospectively registered’, https://clinicaltrials.gov/ct2/show/NCT04946682?term=NCT04946682&draw=2&rank=1

## Background

Encephalitis/meningitis are defined as encephalopathy with associated seizures, neurological dysfunction and focal neurological deficits; there are a wide variety of possible infectious and autoimmune mechanisms [1]. The annual incidence of encephalitis is about 12.6/100,000. Encephalitis/meningitis has a heavy disease burden, and 5–26% of patients suffer from neurological sequelae with a mortality rate of up to 5–10% [1]. Between 40 and 50% of cases with known causes are attributable to infections and of these, viruses are the most common cause, followed by bacteria. In viral infections, *Japanese encephalitis virus* is the most common epidemic virus, and *herpes simplex virus* (HSV) is the most commonly detected sporadic pathogen [2]. Autoimmune encephalitis (AE) accounts for approximately 20–30% of encephalitis/meningitis cases.

The timely identification of causative agents is critical for the administration of effective treatment for infectious encephalitis/meningitis. Multiplex polymerase chain reaction (PCR) sequencing, such as the FilmArray meningitis/encephalitis and Xpert MTB/RIF Ultra panels, are able to improve diagnostic capability in a limited spectrum of pathogens, however this still does not meet clinical needs. Therefore, there is still a need for rapid detection methods with a wide pathogen spectrum in order to improve the diagnostic process of infectious encephalitis [3–6]. In recent years, metagenomic next-generation sequencing (mNGS) has been shown to have great advantages in the diagnosis of infectious diseases, especially in bloodstream, respiratory tract, and central nervous system (CNS) infections. It is proposed that the diagnosis rate of CNS infections can be improved by approximately 25% with the application of mNGS [7]. This process features a short turnaround time, unbiased detection and dynamic surveillance [8]. Application of mNGS may improve and optimize diagnostic strategies for infectious encephalitis/meningitis.

The rapid development of cell-based assays (CBAs), tissue-based assays (TBAs) and B cell repertoire analyses accelerated the discovery of novel autoantibodies and their applications for the diagnosis of AE [9, 10]. CBAs are commonly used in clinical practice, but can only detect a narrow spectrum of autoantibodies that are targeted to currently known antigens. On the other hand, TBAs can facilitate the discovery of unknown autoantibodies [11]. Therefore, the combination of broad-spectrum CBAs and TBAs could be a powerful tool in the diagnosis of autoantibody-associated encephalitis. However, the diagnosis of AE requires the simultaneous exclusion of other possible diseases, thus, it is of great importance to combine nucleic acid amplification testing for infectious agents with autoimmune antibody tests to improve the diagnosis and treatment of encephalitis/meningitis [12, 13]. Moreover, though several diagnostic methods have been used, a recognized and unified diagnosis and treatment process for encephalitis management remains unclear.

Therefore, we propose a multicenter, open label, randomized controlled clinical trial to evaluate the diagnostic performance of a new diagnostic algorithm which combines mNGS and autoimmune antibodies analysis. The impact on the outcomes of the patients enrolled will also be assessed. We hope to develop an optimized process for the diagnosis and treatment of encephalitis/meningitis which will result in more effective treatments.

## Methods

### Study design

This study is a multicenter open label, randomized controlled clinical trial of non-inferiority with two arms recruiting patients with suspected encephalitis/meningitis. The enrolled patients will be grouped into two parallel groups with a ratio of 1:1, those whose diagnoses were achieved through multiplex PCR tests plus autoimmune antibody analyses (Group I), and those being assessed through the use of mNGS plus autoimmune antibody testing (Group II). The detailed study schematic is shown in Fig. 1.

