### Sample size calculation

The predicted sample size was calculated using the PASS 11 software. Assuming hazard ratio (HR) = 1.48 and θ = 1, and according to previous research, pE = 0.7, PA = 0.5, each group requires 230 samples. Assuming a 5% drop-out rate in follow-up, each group needs 230 × 1.05 = 242 people; therefore, the total sample size of the two groups combined is calculated to be 484 people.

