### Assessment and analysis of outcomes

The primary and secondary outcomes between Group I and Group II will be compared. Primary outcomes are the initial time of targeted treatment and mRS score on the 30th day whilst secondary outcomes include CSF index remission rate on the 14th day, mortality rate on the 30th day, and the evaluation of diagnostic efficacy. Through these assessments, we may explore the best diagnostic algorithm for encephalitis/meningitis, and finally determine its optimal treatment.

The results for the trial outcomes will be analyzed through the following methods. First, we will review whether the enrolled cases meet the selection and exclusion criteria, and whether the actual number of enrolled, excluded and dropped cases in each center are accounted for at the end of the study; we will then perform a comparability analysis. Data relating to demographic characteristics, general and baseline (before the test) conditions will be compared between the two groups. The statistical analyses to be employed include two-sided t-tests, Wilcoxon tests, and chi-square tests—which will compare the outcomes between the two groups. A P value ≤ 0.05 was considered statistically significant. Excel was adopted for the management of data and the performance of statistical analysis after verification. SPSS 11.0 and PRISM 9.0 were the software used for statistical analyses.

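### The trial is labelled non-inferiority, but no value is identified as a margin and the stated tests of difference at P ≤ 0.05 do not test that hypothesis

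*Protocol article*

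**What the plan says.** Three sections of the protocol article bear on the hypothesis.

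- **Study design** states: "This study is a multicenter open label, randomized controlled clinical trial of non-inferiority with two arms recruiting patients with suspected encephalitis/meningitis". It does not say which arm is to be shown non-inferior, in which direction, or on which outcome. The design statement in the abstract does not mention non-inferiority.
- **Sample size calculation** gives "Assuming hazard ratio (HR) = 1.48 and θ = 1" and "according to previous research, pE = 0.7, PA = 0.5", from which "each group requires 230 samples". After the drop-out allowance, "the total sample size of the two groups combined is calculated to be 484 people". The symbols θ, pE and PA are not defined, no alpha or power is given, and neither 1.48 nor 1 is called a margin.
- **Assessment and analysis of outcomes** names two primary outcomes, time to first targeted treatment and day-30 mRS. It compares the groups by t-test (declared two-sided), Wilcoxon test and chi-square test. The rule is: "A P value ≤ 0.05 was considered statistically significant". No confidence limit is set against any margin, for either outcome.

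**The concern.** A non-inferiority claim requires that a confidence limit exclude a pre-stated margin. A test of no difference asks another question, and its failure to reach significance may reflect only imprecision. The declared hypothesis and the stated decision rule therefore do not match.

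The mismatch remains under either reading of the sample size. If 1.48 is an assumed effect tested against a null ratio of 1, the design label is wrong. If 1.48 is an unlabelled margin with a true ratio of 1, the decision rule never uses it.

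At stake is the meaning of the primary result: a reader could not tell what a significant or a non-significant P value says about the declared hypothesis. Because the trial is open label, a margin chosen after between-arm results are known would carry little weight.

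**Working it through.** **Inputs.** From the Sample size calculation section: HR = 1.48, θ = 1, pE = 0.7, PA = 0.5, 230 per group. From the outcome analysis section: threshold 0.05. Assumed, because undefined: pE is the overall event probability and PA the share of patients in one arm. Alpha and power for the sample size are not stated, so a range is shown.

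**1. Can the stated 230 per group be reproduced, and does it reveal a margin?** The usual Cox/Schoenfeld formula is

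N(total) = (z_α + z_β)² / [PA(1 − PA) × pE × (ln HR − ln θ)²].

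The denominator is 0.25 × 0.7 × (0.3920)² = 0.02690.

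| Alpha, power (assumed) | (z_α + z_β)² | N total | Per group |
|---|---|---|---|
| two-sided 0.05, 80% | 7.849 | 291.8 | 146 |
| two-sided 0.05, 90% | 10.507 | 390.6 | 195 |
| two-sided 0.05, 95% | 12.995 | 483.1 | 242 |
| one-sided 0.05, 80% | 6.183 | 229.9 | 115 |
| two-sided 0.025, 90% | 12.411 | 461.4 | 230.7 |

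The common two-sided 0.05 settings do not give 230 per group. One-sided 0.05 with 80% power gives 230, but as a total. Two-sided 0.025 with 90% power comes close per group, but the article states neither value. Reproduction therefore cannot be settled.

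The formula also depends only on |ln 1.48 − ln 1|. An effect of 1.48 against a null of 1, and a margin of 1.48 with a true ratio of 1, give the same N. The arithmetic cannot show which was meant.

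**2. What would a non-significant result mean?** Evaluable patients 2 × 230 = 460; events 460 × 0.7 = 322; SE(log HR) = 2/√322 = 0.1115. Let HR below 1 mean slower targeted treatment.

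- True HR 0.80: |ln 0.80|/0.1115 = 2.00, so P(P > 0.05) ≈ Φ(1.96 − 2.00) = 0.48.
- True HR 0.75: |ln 0.75|/0.1115 = 2.58, so P(P > 0.05) ≈ Φ(1.96 − 2.58) = 0.27.

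A materially slower arm would often produce a non-significant test.

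**3. Would 460 patients be enough for non-inferiority?** With true HR = 1, one-sided 0.025, 80% power and 1:1 allocation, events = 4 × 7.849/(ln margin)² and N = events/0.7, before drop-out. Margins are written as ratios above 1; the reciprocal gives the same N.

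| Assumed margin | Events | N total |
|---|---|---|
| 1.2 | 945 | 1350 |
| 1.25 | 631 | 902 |
| 1.3 | 457 | 653 |
| 1.4 | 278 | 398 |
| 1.48 | 205 | 293 |

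The planned 460 lies inside this range: far too few for a tight margin, more than enough for a wide one.

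**The case against.** **The article is a condensation.** The margin, the arm and a confidence-interval method may stand in a full protocol or SAP that is not shown, and the listed tests are not presented as exhaustive. This stands in part: the absence of a margin is not by itself the point. What remains is a conflict between things the article does state, since the declared hypothesis type and the published tests and threshold do not fit each other.

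**A reader might infer that the trial was really sized for superiority of the mNGS arm.** The documents do not support that. The formula is the same under both readings, and two-sided 0.05 at 80, 90 or 95% power does not return 230 per group. The text points both ways. The Background expects mNGS to improve the diagnosis rate by about 25% and hopes for better treatment. The Discussion wants to show that the PCR cassette is fast and inexpensive and stresses cost-effectiveness, which suits a non-inferiority question about the PCR arm.

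**A reader might infer that the trial could never support non-inferiority.** That is too strong. A significant result in favour of the arm to be shown non-inferior would support it, as would a confidence interval compared with a margin fixed in advance. Nor does the article say that P > 0.05 will be read as non-inferiority; that misuse is a risk, not a stated plan.

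**A reader might quote a 35% lower rate of targeted treatment hidden behind a non-significant result.** That figure is the lower 95% limit, exp(−2 × 1.96 × 0.1115) = 0.646, of a result lying exactly on the significance boundary, exp(−1.96 × 0.1115) = 0.804. If the true HR were 0.65, non-significance would occur only about 2.8% of the time (|ln 0.65|/0.1115 = 3.86; Φ(1.96 − 3.86) ≈ 0.028). It should not be the headline.

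**Conclusion.** The point holds in this form: the trial is labelled non-inferiority, no value is identified as a margin, no arm or direction is given, and the stated rule is a set of difference tests that do not test the declared hypothesis. Confidence in this mismatch is high, because it rests on the text alone.

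The 48% (true HR 0.80) and 27% (true HR 0.75) are illustrations. They assume 322 events, pE as the overall event probability, and a log hazard ratio test that the analysis section does not list. The sample-size range in step 3 also rests on assumed margins, alpha and power, and shows only that adequacy cannot be judged without them. Which hypothesis the sponsor intended is open, and superiority should not be imposed by default.

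**What to change.** Reconcile the Study design, Sample size calculation and outcome analysis sections before any between-arm look, in one of two ways.

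- **(a) If non-inferiority is intended:** state the arm, direction and margin for each primary outcome (time to targeted treatment and day-30 mRS). Say whether 1.48 is the margin or the assumed effect, define θ, pE and PA, and give alpha and power. Replace the P ≤ 0.05 rule by a comparison of the confidence limit with the margin.
- **(b) If superiority is intended:** delete the non-inferiority label, state the superiority hypothesis for each primary outcome, report effect estimates with 95% confidence intervals, and state that P > 0.05 is not evidence of similarity.

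**Cost.** Both routes change protocol and analysis wording. Route (b) does not by itself require more patients, although the sample-size basis should still be stated. Under route (a), whether 460 evaluable patients suffice depends on the margin and must be rechecked once it is named.

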**Fig. 1 Fig1:**
[figure not shown]
IMPROVE study outline

### Ethical and confidential considerations

The study protocol and informed consent forms have been approved by the Huashan Hospital Ethical committee (protocol ID: 2021-KY451). The clinician should obtain face to face informed consent during an interview before enrollment. All patients will provide written informed consent.

### Study flowchart and clinical evaluation of enrolled patients

Adult patients who meet the inclusion criteria will be eligible (Table 1). Eligible patients with suspected encephalitis/meningitis will be included after signing the informed consent forms. As outlined above, the participants will be randomly assigned in a 1:1 ratio to Group I or Group II. The randomization is performed through the online central randomization system stratified by the study sites (Clinflash, China). To facilitate autoimmune encephalitis antibody tests and molecular etiological examinations, 13 ml of peripheral blood and 8 ml of cerebrospinal fluid (CSF) will be collected. The first screen will include basic patient characteristic, as well as additional information such as present history, functional assessments (modified Rankin Scale [mRS], Glasgow outcome score [GOS] and EuroQol-5 Dimension (EQ-5D)), physical examinations, cranial magnetic resonance imaging (MRI), blood examinations including routine blood tests, C-reactive protein, synchronous glucose, D-dimer, *Treponema pallidum* particle agglutination assay/rapid plasma reagin, thyroid hormones and thyroid-related antibodies; CSF pressure, biochemical and routine tests; and etiological examinations of CSF including latex agglutination test, ink stain, and bacterial, fungi and tuberculosis cultures. Electroencephalograms are to be performed according to clinical necessity.

**Table 1 Tab1:** Inclusion and exclusion criteria

Inclusion criteria
• Aged from 18 to 80 years old
• Without clear diagnosis
• Without effective antimicrobial therapy
• The suspected meningitis/encephalitis patients should meet the ① or ② items as following:
① Suspected meningitis: Rapid onset fever (> 38.5 °C). with at least one of the three manifestations as following:
(1) Neck stiffness
(2) Alteration of consciousness
(3) Other signs indicating meningitis, for example, meningeal irritation sign
② Suspected encephalitis: Altered consciousness because of unidentified reasons that persisted for longer than 24 h, including lethargy, irritability, or a change in personality, and have at least one of these manifestations:
(1) Fever or history of fever (≥ 38 °C, oral temperature) during the presenting illness
(2) Seizures not explained by a previously known seizure disorder
(3) CSF pleocytosis (white blood cell count of more than 4 cells per μl)
(4) Electroencephalographic (EEG) findings indicative of encephalitis
(5) Abnormal results of neuroimaging (CT or MRI) suggestive of encephalitis
• Have an identifiable address and resided in the area during treatment
• Willing to participate in the treatment and follow-up and able to provide informed consent (if subject is illiterate, legal guardian sign or consent is required)
• Willing to comply follow-up procedures
Exclusion criteria (≥ 1 items)
**•** Lactation or pregnancy
• Fail to comply follow-up or treatment
• Researchers consider it is unsafe for participant
• No enough blood or CSF samples

For both Group I and II, patients who have positive pathogenic results are considered to have the infectious disease, and those with positive autoimmune encephalitis antibodies are classified as having autoimmune encephalitis; other diseases are confirmed by their corresponding gold standard tests and classified as “other diseases” and the remaining subjects are categorized as being of unknown origin.

Patients with infections of unknown origin are divided into severe encephalitis/meningitis and mild encephalitis/meningitis based on their clinical manifestations. Patients with severe encephalitis/meningitis should meet at least one of five criteria: (1) Disturbance of consciousness: GOS < 8; (2) New onset of epilepsy or epileptic status; (3) Respiratory failure requiring mechanical ventilation and support; (4) Circulatory failure with vasoactive drug use; (5) Complicated multiple organ failure requiring intensive care unit monitoring and treatment. If a patient in Group I develops severe encephalitis/meningitis with an unclear cause after empirical treatment is given, mNGS could be conducted between the 3rd and 14th day of the trial.

Several additional examinations are recommended for patients with infections of unknown origin in both Group I and II. These analyses include CSF Xpert TB/RIF, extended antibody spectrum and paraneoplastic antibody screening, and examination for tumors, congenital, metabolic and cerebrovascular diseases; poisoning, and so on. Targeted treatment should be applied according to test results.

Both groups will be followed up for 12 months and the final diagnosis will be made by doctors at the treating hospital and by physicians of Huashan Hospital which is affiliated with Fudan University.

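### An exclusion item worded as non-compliance, paired with an end-of-study eligibility review, leaves room to exclude randomised patients for what happened after allocation

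*Protocol article*

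**What the plan says.** All references are to the protocol article.

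- **Table 1, exclusion criteria.** The list is headed "Exclusion criteria (≥ 1 items", so a single item excludes. One item is "Fail to comply follow-up or treatment" and another is "No enough blood or CSF samples".
- **Table 1, inclusion criteria.** Willingness is already covered by two items: one on taking part in treatment and follow-up, and "Willing to comply follow-up procedures".
- **Study flowchart and clinical evaluation of enrolled patients.** "Eligible patients with suspected encephalitis/meningitis will be included after signing the informed consent forms", after which "the participants will be randomly assigned in a 1:1 ratio to Group I or Group II".
- **Assessment and analysis of outcomes.** The analysis begins: "First, we will review whether the enrolled cases meet the selection and exclusion criteria". The same sentence adds a check on whether "the actual number of enrolled, excluded and dropped cases in each center are accounted for at the end of the study". A comparability analysis and the outcome tests follow.

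**The concern.** Whether a patient has failed to comply with follow-up or treatment can be observed only once follow-up or treatment is under way, which is after randomisation. As an exclusion item it is harmless if it is applied only at screening. It matters here because the criteria are consulted again at the start of the outcome analysis, when compliance is known, and because excluded cases are counted apart from dropped ones at study end.

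If a patient is taken out of the comparison at that stage, the groups compared are no longer the groups randomised. Patients and clinicians know the arm, so compliance, transfer and the judgement that someone did not comply can all depend on it. They can also depend on whether the patient is deteriorating or recovering. Time to targeted treatment, day-30 mRS and 30-day mortality are all exposed.

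**Working it through.** **1. Reading the passages together.**

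- The exclusion item is worded as a fact (failing to comply), not as an expectation at screening. Nothing in the article restricts it to baseline.
- A purely baseline reading would add little, since two inclusion items already ask for willingness.
- The review in the outcome section concerns cases already enrolled and uses the full set of criteria. It is not limited to information available at randomisation.
- Excluded and dropped cases are separate categories in the end-of-study accounting. A patient who does not comply with follow-up could be placed in either.

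The literal reading is therefore open. No sentence states it as a rule, and no sentence closes it.

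**2. The plan's own figures.** Sample size calculation gives 230 per group with a 5% dropout allowance: 230 × 1.05 = 241.5, so 242 per group, and 2 × 242 = 484. This agrees with the article. The sample size is not in dispute; 242 is used below only as the arm size.

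**3. How removal shifts an observed proportion.** Let p be the true proportion with an outcome in an arm, r the fraction of the arm removed, and q the proportion with the outcome among those removed.

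Observed proportion = (p − r·q)/(1 − r), so the shift is r·(p − q)/(1 − r).

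The shift is zero only if nobody is removed or those removed resemble the rest (q = p). Its sign depends on whether q is below or above p, so the direction cannot be known in advance.

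**4. Illustration.** The removal rates and q are assumptions. So is p = 0.60 in both arms (no true difference), chosen as the midpoint of the two proportions in the sample-size text: (0.7 + 0.5)/2. The test is a two-sided 5% comparison of two proportions, with q equal in both arms.

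| Removed, arm A / arm B | q | Observed A | Observed B | Spurious difference | Type I error |
|---|---|---|---|---|---|
| 5% / 5% | 0 | 0.632 | 0.632 | 0 | 5% |
| 5% / 5% | 0.3 | 0.616 | 0.616 | 0 | 5% |
| 5% / 10% | 0 | 0.632 | 0.667 | 3.5 points | 12.2% |
| 5% / 10% | 0.3 | 0.616 | 0.633 | 1.8 points | 6.7% |
| 5% / 15% | 0 | 0.632 | 0.706 | 7.4 points | 37.6% |
| 5% / 15% | 0.3 | 0.616 | 0.653 | 3.7 points | 12.7% |

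Worked row (5% / 15%, q = 0):

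- Arm A: 0.60/0.95 = 0.632 on 242 × 0.95 = 229.9 patients.
- Arm B: 0.60/0.85 = 0.706 on 242 × 0.85 = 205.7 patients.
- Pooled proportion 0.667; standard error = √[0.667 × 0.333 × (1/229.9 + 1/205.7)] = 0.045.
- 0.074/0.045 is about 1.64 standard errors, so the rejection probability is P(Z > 1.96 − 1.64) plus a negligible lower tail, or 0.376.

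Equal removal is harmless to the type I error here only because the same kind of patient is removed from both arms. Equal rates with different kinds of patient removed would still bias the comparison.

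**The case against.** Table 1 is an eligibility table, introduced before consent and randomisation. In that place the item may be loose wording for a patient unlikely to comply. That it would then repeat the willingness items proves little, because the inclusion list already repeats itself. The outcome section speaks of reviewing and accounting, which may be no more than a deviation check and a participant-flow count, and excluded may mean excluded at screening. The section Data collection and quality management also says that every case meeting the inclusion criteria must be included and may not be omitted.

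Much of this stands. A reader might infer that the plan deletes non-compliant patients. The article does not say so, and the point here is only that its wording permits it. The rule against omitting cases concerns enrolment, however, and does not say how an enrolled patient who later fails to comply is handled.

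A reader might also infer that study samples are taken after randomisation, because the flowchart section mentions them in that order. Sentence order does not establish this: the same paragraph describes the first screen later still. Adverse event management says the extra volumes are drawn during routine examinations, and CSF pleocytosis is one of the qualifying findings for suspected encephalitis. Nor does the article support the idea that the sample requirement differs by arm, since it gives one volume of blood and one of CSF for all participants. What remains is that the sample item has no stated time of judgement.

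Finally, a definition of analysis sets may sit in the full protocol or SAP, and its absence from the article is no defect. But a set defined by meeting the eligibility criteria would inherit this wording.

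**Conclusion.** The point holds as one of badly fixed wording: a criterion that literally describes post-randomisation behaviour is tied to a review of enrolled cases at the analysis stage. It does not show that exclusions will occur.

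The size and direction of any bias are unknown. The range of 3.7 to 7.4 points, with a type I error of about 13% to 38%, rests on an assumed 60% outcome rate, removal of 5% versus 15%, and 0 to 30% of those removed having the outcome. With 5% versus 10% it falls to 1.8 to 3.5 points and about 7% to 12%. With equal removal unrelated to arm the type I error stays at about 5%.

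The 5% in the sample-size section should not be read as an expected exclusion rate. It is an allowance for dropout in follow-up, and outcomes that were never observed would not be recovered by rewording Table 1.

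**What to change.** Four changes of wording:

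1. In Table 1, recast the compliance item as a judgement made before randomisation, for example: judged unable to comply with follow-up.
2. State that sufficiency of blood and CSF samples is also judged before allocation.
3. In Assessment and analysis of outcomes, restrict the eligibility review to facts known before randomisation, and say whether excluded means excluded at screening.
4. State that later non-compliance is not a reason to remove a patient from the randomised comparison, and that an analysis leaving such patients out is a sensitivity analysis only.

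The cost is a short text amendment. Item 2 changes practice only at a site that now randomises before samples are confirmed. No change to the sample size is needed.

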### Duration of follow-up

Follow up will take place on the 7th and 14th day and in the 3rd, 6th and 12th month of the trial. Follow-up examinations will mainly consist of clinical evaluation, physical examination, routine blood examinations including routine blood parameters, C-reactive protein, D-dimer, and synchronized glucose; CSF examinations such as pressure, biochemical and routine tests; nervous system analysis scores including mRS, GOS Score and EQ-5D; extra autoimmune encephalitis antibody tests and molecular etiology examination.

According to these examinations, if symptoms persist or the condition of the participant is worse between the 15th and 60th day, we may reperform additional autoimmune encephalitis antibody tests and molecular etiology examinations (mNGS test).

In summary, detailed follow up examination will proceed in the following order; clinical evaluation, physical examination and nervous system analysis scores should be evaluated on the 7th and 14th day of the trial. In addition, a lumbar puncture and routine blood examination should also be conducted on these days, and CSF will be subjected to autoimmune encephalitis antibody tests (Table 2). Assessments in the 3rd and 12th month will involve clinical evaluation, physical examination, and nervous system analysis scores.

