## Abbreviations

AE: Autoimmune encephalitis
CBA: Cell-based assay
CEP: California Encephalitis Project
CNS: Central nervous system
CSF: Cerebrospinal fluid
GOS: Glasgow outcome score
HSV: Herpes simplex virus
MRI: Magnetic resonance imaging
mNGS: Metagenomic next-generation sequencing
mRS: Modified Rankin scale
PCR: Polymerase chain reaction
TBA: Tissue-based assay
CRF: Case report form
HR: Hazard ratio

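### Severity criterion (1) puts a cut-off of 8 on the Glasgow outcome score, which does not separate severe from mild among patients with disturbed consciousness

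*Protocol article*

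**What the plan says.** Under *Study flowchart and clinical evaluation of enrolled patients*, patients whose infection is of unknown origin are split into severe and mild. The rule is "Patients with severe encephalitis/meningitis should meet at least one of five criteria", and the first of the five is "1) Disturbance of consciousness: GOS < 8".

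The abbreviation is explained in two places, both times the same way. The baseline assessments in that section include "functional assessments (modified Rankin Scale [mRS], Glasgow outcome score [GOS] and EuroQol-5 Dimension (EQ-5D", and the *Abbreviations* list has "GOS: Glasgow outcome score". *Duration of follow-up* uses it in the same sense, among "nervous system analysis scores including mRS, GOS Score and EQ-5D". No coma or level-of-consciousness scale is named anywhere in the article, and no range is given for GOS.

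The severity class has a consequence. If a Group I patient "develops severe encephalitis/meningitis with an unclear cause after empirical treatment is given, mNGS could be conducted between the 3rd and 14th day".

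**The concern.** A criterion headed as disturbance of consciousness is measured with a functional outcome score, at a cut-off that appears to lie at or above the top of that score. If so, the number adds almost nothing to the heading: any patient with disturbed consciousness counts as severe, however slight the disturbance.

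Severity is part of the gate through which Group I patients may receive the test that defines Group II. The gate operates on days 3–14, before the day-30 mRS (a primary outcome) and day-30 mortality (secondary). In patients not yet on targeted treatment it can also affect the other primary outcome, the initial time of targeted treatment. Looser access to mNGS in Group I can pull the arms together. Because *Study design* describes the trial as non-inferiority, such convergence would tend to favour the trial's conclusion. Sites that read the criterion differently would also apply different rescue rules.

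**Working it through.** The article states no figure to reproduce, and no sample size, power or alpha depends on this criterion. The check is to count how many levels of each candidate scale fall below 8, and then to see which patients the criterion sorts.

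**Inputs from the article**
- Cut-off: below 8, under the heading of disturbed consciousness (*Study flowchart and clinical evaluation of enrolled patients*).
- Instrument: Glasgow outcome score (same section, and *Abbreviations*).
- Combination rule: any one of five criteria makes a patient severe.
- Rescue window: days 3–14, Group I, cause unclear after empirical treatment.

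**Inputs assumed, because the article gives no ranges**
- Standard outcome score: 1–5.
- Extended outcome score: 1–8.
- Coma scale, as the likely intended instrument: 3–15.

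**Count.** Number of levels = maximum − minimum + 1. Levels meeting the criterion = those below 8.

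| Scale (assumed range) | Levels in total | Levels below 8 | Share |
|---|---|---|---|
| Outcome score, 1–5 | 5 − 1 + 1 = 5 | 1 to 5, so 5 | 5/5 = 100% |
| Extended outcome score, 1–8 | 8 − 1 + 1 = 8 | 1 to 7, so 7 | 7/8 = 87.5% |
| Coma scale, 3–15 | 15 − 3 + 1 = 13 | 3 to 7, so 5 | 5/13 = 38% |

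These are shares of scale levels, not of patients. On the extended score the one level that escapes is the best recovery category, which a patient with disturbed consciousness would not plausibly be given. Both versions of the named instrument therefore lead to the same result. On the coma scale, 8 of 13 levels (8 to 15) would remain not severe, so the cut-off would do its job.

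**Which patients are affected.** The heading still does some work: someone who entered by the meningitis route with fever and neck stiffness only, and normal consciousness, does not meet criterion (1). Entry by the encephalitis route is different, because Table 1 requires "Altered consciousness because of unidentified reasons that persisted for longer than 24 h, including lethargy, irritability, or a change in personality". Any such patient who is still of unknown origin and whose consciousness has not recovered meets criterion (1) as written, whether lethargic or comatose.

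**Timing.** "nervous system analysis scores should be evaluated on the 7th and 14th day of the trial", so outcome scores are due on two days inside the day 3–14 window. A site following the text would have a recorded GOS to apply; no consciousness scale is listed for collection.

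**The case against.** The strongest reply is that this is an obvious slip. A clinician would see that 8 is impossible on a five-level scale, would read the heading, and would use a coma scale. *Data collection and quality management* describes uniform training, central review of each case and supervision every two months, all of which could catch it. The gate is also narrower than the cut-off alone suggests: it covers only patients of unknown origin, it speaks of a patient developing severe disease, which may imply worsening, and the test remains optional. Rescue mNGS is a deliberate design feature, and *Duration of follow-up* separately allows mNGS between days 15 and 60 for persistent or worsening illness with no GOS condition. Some crossover would therefore exist even with a perfect criterion.

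Much of this stands as a limit on the size of the problem. Many clinicians probably will read a coma scale, and only the added crossover due to criterion (1) is at issue. It does not remove the error. The abbreviation is defined twice as the outcome score, and no alternative instrument is named, so training and review have no correct written criterion in the article to enforce. Worsening would be judged against the same five criteria, so the faulty cut-off applies there too. Nor is this a detail left to a fuller document: the article states a specific instrument and number, and they do not fit together.

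**Conclusion.** The criterion is wrong as written and should be fixed. On either assumed range of the named score, the cut-off is met at 5 of 5 or 7 of 8 levels and does essentially no sorting among patients with disturbed consciousness. It does not make every enrolled patient severe, since those with normal consciousness are still excluded by the heading.

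The conclusion rests on the assumed ranges of the outcome score. That a 3–15 coma scale was intended is likely but unconfirmed. The number of additional Group I patients who would receive mNGS, and the resulting effect on the day-30 outcomes, cannot be derived from the article.

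**What to change.** In criterion (1), replace the GOS cut-off with the intended level-of-consciousness instrument and its threshold, confirmed by the sponsor. Write the instrument's name in full so that it cannot be confused with the Glasgow outcome score, and add it to the assessments listed at baseline and in *Duration of follow-up*. If a 3–15 coma scale with a cut-off below 8 is confirmed, scores 3–7 would be severe on this criterion and 8–15 would not.

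It would also help, though it is not essential, to record which of the five criteria triggered each rescue mNGS, so that crossover can be described by cause. The cost is a one-line protocol correction, a matching entry in the assessment lists and, for the optional part, one CRF field.
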